**Fig. 1 Fig1:**
[figure not shown]
Study Flow

### Participants

Participants are patients, staff and referrers to the sleep centre. The inclusion and exclusion criteria are broad in order to maximize the generalizability and applicability of our results to the real-world health care context.

#### Patients

Consecutive patients attending the Sleep Psychology service from 1 January 2021. Inclusion criteria will include all NEW patient referrals to the Sleep Disorders Service at the Prince Charles Hospital in Brisbane, Australia who would have been referred to Sleep Psychology at some point in their patient journey from 1 January 2021 until 31 December 2024. Data collection will continue until December 2025 as patients filter through the treatment model. Exclusion criteria will include any patients referred prior to 1 January 2021 or after completion of the study.

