## Methods

### Aims and objectives

The overarching aim of the current study is to evaluate the impact of adopting a new Direct to Psychology Stepped Care Model into the multidisciplinary sleep service. The model of care will incorporate a “Direct to Psychology Insomnia” referral pathway, with a “Stepped Care” treatment approach that utilises digital, group, trainee and clinician level interventions, flexibly delivered across the continuum of care. The RE-AIM Framework [20, 21] will be adopted to evaluate individual and service level outcomes in a pre- post study design comparing Standard Care to Direct to Psychology Stepped Care. The objective is to capture all service events, clinical outcomes and quality of life changes for patients referred to the sleep psychology service in order to perform a full evaluation including a cost effectiveness analysis.

The specific hypotheses include the following:

Compared to Standard Care, the Direct to Psychology Stepped Care Model will be associated with:Reduced wait times and improved access to treatmentEquivalent (non-inferior) clinical outcomes and changes in quality of lifeService delivery that is less resource intensive and delivered at a lower cost

In addition, we hypothesize that stakeholders (referrer, patient, staff) will be satisfied with the service changes.

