### Design and setting

This project will employ a single-site, multi-phase, mixed-methods approach to evaluate the implementation of the new model of care into the Sleep Psychology service in a tertiary public hospital, embedded within the RE-AIM implementation evaluation framework [19, 20, 22]. Reporting will align with the Standards for intervention Reporting Implementation Studies (STaRI) framework [23]. Patient, service-level and implementation outcomes will be evaluated by comparing patients attending the service from 1 January 2021 until 30 June 2023 as a pre-measure (old model of care) to patients attending the service from implementation of the model from 1 July 2023 to 31 December 2024 as a post-measure (new model of care). This project has received ethics approval via the low and negligible risk pathway with a waiver of informed consent with the Darling Downs Human Research Ethics Committee (HREC 2022 QTDD 88350). Figure 1 outlines the study flow.

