### Intervention

#### Standard care

An exploratory qualitative analysis of consumer and stakeholder perspectives to benchmark the existing service was undertaken, followed by stakeholder consensus groups that informed the new model of care parameters including inclusion and exclusion criteria for the Direct to Psychology Pathway [24], and inclusion and exclusion criteria for assigning patients to the ‘steps’ of the stepped care model [25]. In the new Model of Care, all new referrals to the Sleep Disorders Centre will be triaged by a Sleep Physician (as per current practice) and referrals will then be directed to either Standard Care and waitlisted for a Sleep Physician initial consultation, or to the “Direct to Psychology” pathway. Note that referrals to psychology will also be accepted via the Standard Care pathway for patients requiring a medical first contact and directed to the appropriate Stepped Care treatment option.

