*How effective was the model of care in achieving its intended outcomes?*	**Effectiveness** – impact on outcomes and quality of life/economic outcomes	**Primary outcomes** *Service Access Measures* • Average number of occasions of Service within Sleep Psychology service under ‘old’ model compared to ‘new’ model of care • Percentage of new patient activity under ‘old’ model compared to ‘new’ model of care • Average wait-time to access a first appointment with Sleep Psychology from date of referral under ‘old’ model compared to ‘new’ model of care • Average time to discharge from first appointment to final appointment with Sleep Psychology under ‘old’ model compared to ‘new’ model of care • Percentage of patients discharged from psychology *Patient-related Outcomes* • Change scores on clinical outcome measures pre- to post- treatment on clinical outcome measures (ISI, DASS-21, K10 and EQ-5D-5 L) comparing patients treated under ‘old’ model versus ‘new’ model of care • % patients treated adequately at each level of Stepped Care • Differences in patient characteristics (age, sex, geographical location, presenting issue) between those who are adequately treated at each level of the new model of care (moderation analysis) *Economic Outcomes* • Quality-adjusted life year calculations as a measure of cost-effectiveness of the ‘new’ model of care compared to the ‘old’ model of standard care **Secondary outcomes** *Patient satisfaction* • Patient satisfaction measure (SRS) post- treatment comparing patients treated under ‘old’ model versus ‘new’ model of care *Patient satisfaction with digital intervention* • Patient reported ease of access to digital intervention • Acceptability and relatability of the online program/service provided (rated by patients), including: i. motivation to access online treatment (diversion from public hospital services for insomnia treatment) ii. understanding of intervention materials iv. perceived change in sleep problem • Differences in patient characteristics (age, sex, geographical location, presenting issue) between those who complete the digital intervention compared to those who do not complete	Significantly fewer occasions of service under new model of care Significantly greater % new patient appointments under new model Significantly shorter wait-time to first appointment under new model Significantly shorter time to discharge under new model Outcomes are non-inferior under new model of care; upper bound 95%CI on outcome measures is less than MCID MCID is achieved on outcome measures by > 80% patients at each level The ‘new’ model is more cost effective Patient reported satisfaction is non-inferior under new model of care; upper bound 95%CI is less than MCID > 90% patients report positive experiences	Patient qualitative and quantitative surveys Medical Record Patient registration system

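### The access cohort is defined both by attendance and by referral, and under either definition waits exist only for patients who were seen, with no old-versus-new measure of the share of suitable referrals reaching psychology

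*Protocol article*

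**What the plan says.** Two definitions of the compared patients stand side by side in the protocol article.

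- **By attendance.** Design and setting states: "Patient, service-level and implementation outcomes will be evaluated by comparing patients attending the service", with the old model running to 30 June 2023 and the new model from 1 July 2023 to 31 December 2024. The Patients section opens in the same way: "Consecutive patients attending the Sleep Psychology service from 1 January 2021".
- **By referral.** The next sentence of the Patients section takes new referrals to the Sleep Disorders Service "who would have been referred to Sleep Psychology at some point in their patient journey from 1 January 2021 until 31 December 2024", and the exclusion there is by referral date. Aims and objectives likewise sets out to "capture all service events, clinical outcomes and quality of life changes for patients referred to the sleep psychology service".

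The first hypothesis is that the new model shortens waits and improves access to treatment. The matching measure in Table 1 is "Average wait-time to access a first appointment with Sleep Psychology from date of referral". Service access measures words it as time from referral to the start of treatment. Statistical analysis forms four groups (period by Direct to Psychology eligibility) and compares their waits by one-way ANOVA and linear regression.

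**The concern.** A wait to first appointment has no value for someone who was never seen. Under the old model, a patient suitable for psychology first had to pass the physician step, which the Background says delays care. Under the new model, triage can send that patient straight to psychology, and only the others are "waitlisted for a Sleep Physician initial consultation". A longer path gives more time to drop off the list, and dropping off is tied to the length of wait being measured. The loss is therefore likely to be unequal in the contrast that matters most, eligible patients before versus eligible patients after.

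Two things are at stake: the size of the estimated reduction in wait, and whether a gain in the share of suitable patients who reach psychology would be seen at all.

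**Working it through.** **1. Does any listed old-versus-new measure supply the missing denominator?**

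- New patient activity and occasions of service: volumes, with no denominator of suitable referrals.
- Percentage discharged from psychology: concerns patients already in psychology.
- Reach, share of direct referrals who stay on the pathway: new model only.
- Adoption, share of eligible patients sent to the pathway: measures being referred, not arriving.

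None is the proportion of suitable referrals that reach psychology in each period.

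**2. The plan's own figure.** The article gives no waits or removal rates to reproduce. The only figure attached to the wait analysis is its power: 80% for 220 patients, four groups, f = 0.25, alpha 0.05. The noncentral F with noncentrality 220 × 0.25² = 13.75 and 3 and 216 degrees of freedom gives 88.4%. 180 patients would give 80.4%, and 180/(1 − 0.18) ≈ 220, so the total may already include the allowance for incomplete data. This does not affect who enters the comparison.

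**3. Size under assumptions.** All inputs here are assumed. Waits are gamma with mean m and coefficient of variation CV (shape k = 1/CV², scale θ = m/k). Removal from the list is exponential at rate λ per month, the same in both models and independent of the patient's own wait. Then

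- P(seen) = (1 + θλ)^(−k)
- mean wait among those seen = k/(1/θ + λ)

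With true means of 12 (old) and 4 (new) months and λ = 0.03:

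- CV 0.5: k = 4, θ = 3 and 1. P(seen) = 1.09^(−4) = 0.71 and 1.03^(−4) = 0.89. Means are 4/(0.3333 + 0.03) = 11.01 and 4/1.03 = 3.88. Apparent reduction 7.13 against 8 months, −11%.
- CV 0.7: k = 2.041, θ = 5.88 and 1.96. P(seen) = 0.72 and 0.89. Means 10.20 and 3.78. Apparent reduction 6.42 months, −20%.

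In both cases a gain of 17 to 18 percentage points in the share reaching psychology is not measured.

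Error in the raw difference in months over a wider range:

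| Old/new mean (months) | CV | λ = 1% | λ = 3% | λ = 5% |
|---|---|---|---|---|
| 6/3 | 0.5 | −2% | −6% | −10% |
| 6/3 | 0.7 | −4% | −12% | −19% |
| 12/4 | 0.5 | −4% | −11% | −17% |
| 12/4 | 0.7 | −7% | −20% | −30% |
| 18/6 | 0.5 | −6% | −16% | −24% |
| 18/6 | 0.7 | −11% | −27% | −39% |

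**4. Effect on the standardised difference.** In this model the waits of those seen stay gamma with the same CV, so SDs shrink with the means. Dividing by the root mean square of the two SDs, the 12/4, λ = 0.03 case moves from 1.79 to 1.73 (CV 0.5, about −3.5%) and from 1.28 to 1.19 (CV 0.7, about −7%).

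**5. A simpler cross-check.** With exponential waits and competing exponential loss, the mean among those seen is the true mean × (1 − share lost). For an assumed true mean of 12 months and 10%, 20%, 30% or 40% lost, it is 10.8, 9.6, 8.4 or 7.2 months. The 110 patients expected per period, if all had been seen, would then correspond to about 123, 138, 158 or 184 suitable referrals.

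**The case against.** The strongest reply is that the inclusion criterion is already referral-based, so the sentence about attenders is only a lead-in. This stands in part. A reader might infer that the plan keeps only patients who reached psychology, and the Patients section does not support that. What remains is a conflict between sections, together with a wait outcome that is empty for non-attenders under either wording.

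Second, a reader might infer that access is tested only in people who obtained it. That goes too far: new patient activity is a primary access measure at service level and would register higher throughput. It does not show what share of suitable referrals got through.

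Third, the Table 1 target is a significantly shorter wait. The standardised difference moves little in the central case, and the bias as modelled runs against the new model, so it would not manufacture a benefit. This stands. The concern is a misstated effect and an untested part of the hypothesis, not a false positive.

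Fourth, one might infer that the clinical non-inferiority comparison is biased because old-model patients had to persist through the medical queue. The documents give nothing on direction or size, and change scores need treated patients under any cohort definition. No such claim is made here.

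Finally, the choice of time-to-event model could be left to a fuller document. That is fair for the details, but the conflicting cohort definitions and the comparison of mean waits are stated in the article itself.

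**Conclusion.** The point holds in a limited form. Design and setting and the first sentence of the Patients section define the groups by attendance; the inclusion criterion and Aims and objectives define them by referral. Under either, suitable patients who leave before a first appointment drop out of the wait comparison, and no measure compares the proportion reaching psychology between models. The access hypothesis is therefore only partly tested even if the plan is followed exactly.

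That the loss is heavier under the medical-first model is an inference from its extra step, not a documented fact. If so, the new model's benefit on waits tends to be understated: by about 2% to 39% in months over the assumed range, and by less on the standardised scale. These figures depend entirely on the assumed waits, CVs and removal rates, on equal removal rates in the two models, and on removal being independent of the patient's own wait. They apply to patients eligible for Direct to Psychology, since others keep the physician-first route.

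**What to change.** - Reconcile Design and setting with the Patients section. Define both access cohorts by referral date, with Direct to Psychology eligibility judged from the referral information in the same way in both periods, whether or not the patient later attended.
- Report, for each period, the proportion reaching a first psychology appointment (or treatment start) by fixed times such as 6 and 12 months.
- Analyse time from referral by cumulative incidence, with removal or discharge before psychology as a competing event and patients still waiting censored.
- Keep mean wait among attenders as a descriptive measure.

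The cost is modest. Inclusion is already worded by referral, consent is waived, the patient registration system is a named data source, and the four-group analysis already needs eligibility classified in both periods. There are two drawbacks. Referrals that never attended must be classified without the screening done at the psychology assessment (Direct to psychology stepped care). Removal dates must also be extracted from the registration system, and their availability there is an assumption.

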#### Staff

Clinicians and team members, who agree to participate in our surveys.

#### Referrers

All referrers linked to patients included in the project, who respond to our surveys.

### Intervention

#### Standard care

An exploratory qualitative analysis of consumer and stakeholder perspectives to benchmark the existing service was undertaken, followed by stakeholder consensus groups that informed the new model of care parameters including inclusion and exclusion criteria for the Direct to Psychology Pathway [24], and inclusion and exclusion criteria for assigning patients to the ‘steps’ of the stepped care model [25]. In the new Model of Care, all new referrals to the Sleep Disorders Centre will be triaged by a Sleep Physician (as per current practice) and referrals will then be directed to either Standard Care and waitlisted for a Sleep Physician initial consultation, or to the “Direct to Psychology” pathway. Note that referrals to psychology will also be accepted via the Standard Care pathway for patients requiring a medical first contact and directed to the appropriate Stepped Care treatment option.

#### Direct to psychology stepped care

All patients referred to sleep psychology will complete an initial assessment according to Diagnostic and Statistical Manual (DSM-V-tr) and International Classification of Diseases (ICD-11) criteria [26, 27], including outcome measures (see *Measures).* For patients referred ‘Direct to Psychology’ additional measures will manage any potential risks associated with psychology as first contact within the model due to potential ‘missed’ medical clinical indications. These measures will include screening tools for Obstructive Sleep Apnoea (OSA) (using items from the STOP-BANG [28] and Berlin Apnoea [29] Questionnaires), hypersomnolence disorders (using items from the Cataplexy Questionnaire [30] and questions related to the presence of neuromuscular conditions, respiratory conditions and driving risk.

The inclusion criteria for Direct to Psychology criteria as defined in stakeholder co-design activities [24] include;

(i)being referred for insomnia and/or sleep psychology, and/or(ii)suboptimal adherence to OSA treatment including continuous positive airway pressure therapy (CPAP) or mandibular enhancement splint (MAS) if medical management has been already optimised.

Exclusion criteria include;

(i)significant new/changed sleep disordered breathing (or identified significant sleep disordered breathing)(ii)highly comorbid patients (e.g., neuromuscular conditions/weakness, respiratory conditions), diagnosis of hypersomnia/question of central disorder of hypersomnolence(iii)category 1 (urgent) referrals(iv)driving risk.

Patients identified as meeting the inclusion and exclusion criteria will proceed with Psychology-first intervention as indicated. Patients who meet the exclusion will be redirected back to the Standard Care model and may be re-triaged by the attending medical officer based on the additional information gleaned from the psychological assessment.

Patients progressing to psychological treatment will be matched to the appropriate treatment level. Depending on patient engagement and participation with the treatment level, as well as clinical outcomes on key assessment measures; discharge, on-referral and/or entry to another intervention level will be provided. The proposed steps of care in the new model are outlined in Fig. 2.

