##### Patient-related outcomes

Patient-related primary outcomes will test non-inferiority in change scores on key clinical outcome measures from pre- to post- intervention when comparing those patients treated under the old model care compared to those treated under the new model of care. Furthermore, % patients treated adequately at each step of the Stepped Care Model will be measured by the number of patients discharged from the service by the treating clinician with outcome measures indicating reliable clinical change from pre- to post- intervention. The Clinical outcome measures include the Insomnia Severity Index (ISI) [34], Depression Anxiety and Stress Scale (DASS-21) [35], Kessler Psychological Distress Scale (K10) [36], and the EuroQol (EQ-5D-5 L) [37].

**Insomnia Severity Index** (ISI) is a 7-item self-report questionnaire assessing the nature, severity, and impact of insomnia over the past two weeks on a 5-point scale from 0 = no problem; 4 = very severe problem. The measure is widely used in the literature as well as clinically where a score of 11 is indicative of likely meeting criteria for an insomnia disorder in clinical trials and a change score greater than 8 is the minimally important difference to be considered ‘markedly improved’ or in remission [34, 38].

**Depression Anxiety and Stress Scale** (DASS-21) is a short version of a 42-item self-report instrument designed to measure three related negative emotional states: depression, anxiety and tension/stress over the past 7 days. Items are scored on a 3-point scale from 0 (did not apply to me at all) to 3 (applied to me very much, or most of the time). Total scores represent symptoms of distress in each of the domains in the ‘normal’, ‘mild’, ‘moderate’, ‘severe’ and ‘extremely severe’ relative to population norms [35].

**Kessler Psychological Distress Scale** (K10): The K10 is a 10-item self-report scale to assess symptoms over the past 4 weeks. Items are rated on a 5-point scale from 1 (none of the time) to 5 (all of the time). A score of less than 20 represents low psychological distress ‘likely to be mentally well’. Between 20 and 24 represents moderate distress ‘may have a mild mental disorder’ and between 25 and 29 represents high psychological distress ‘likely to have a moderate mental disorder’ [36].

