### Statistical analysis

The project will employ a mixed methods approach. Qualitative surveys for patients, multidisciplinary staff, and referrers was undertaken pre-service change to ascertain the acceptability of the digital therapy, as well as familiarity, access, confidence, and relatability of this treatment option [25]. Post-implementation surveys will also be undertaken on these same metrics. Quantitative data will be collected pre- and post-service change to ascertain treatment effectiveness in terms of clinical outcome measures, as well as service measures of interest such as patient flow, occasions of service and program engagement. Based on similar studies [40], and allowing for some incomplete data, we expect to have data for approximately 110 participants from each pre- and post- time period, resulting in a sample of 220 participants overall who will be suitable for the Direct to Psychology pathway. To assess wait times, participants will be categorised into four groups based on the time-period (pre/post implementation) and whether they met eligibility criteria for the Direct to Psychology pathway. Differences in wait times between the groups will be assessed using a one-way Analysis of Variance (ANOVA) and linear regression modelling. In a one-way ANOVA study, a sample of 220 participants, divided by 4 groups, achieves 80% power with a significance level of 0.05 to detect a moderate-large effect size (Cohen’s f) of 0.25 [41]. The effects of other variables of interest and potential confounders (patient characteristics, diagnosis,) will be tested in multivariable models. For differences in patient outcome measures pre- and post- intervention when comparing pre- and post- service change, the mean between-group difference and 95% confidence interval (CI) will be calculated. As this aspect of the evaluation is a non-inferiority trial (that is, we expect clinical outcomes to not be reduced due to the service change), the criteria adopted to determine non-inferiority will be if the upper bound 95%CI on each clinical outcome measure was less than the minimal clinical important difference (MCID). Quantitative data measuring pre- and post- service change outcomes on key indices of patient service satisfaction, service characteristics (e.g., occasions of service); as well as referrer and staff service satisfaction, and engagement with digital therapies, will be evaluated via univariate statistical tests where indicated such as independent samples t-test (or nonparametric equivalent), and categorical comparisons will be evaluated using Pearson’s chi-square. The distribution of outcome measures will be assessed, and appropriate transformations will be applied for use in modelling. Differences between group means will be tested using generalised linear regression modelling. Health related quality of life will be measured pre- and post- implementation using the EQ-5D-5 L. Population norms for EQ-5D-5 L Australia will be used to value the data set [42].

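### Non-inferiority on ISI, K10 and DASS-21 and the >80% MCID target carry no baseline condition, so patients with little room to change may mask a loss and cap the achievable response

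*Protocol article*

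**What the plan says.** **Who is evaluated.** Under Patients, the article states: "Inclusion criteria will include all NEW patient referrals to the Sleep Disorders Service", limited to those "who would have been referred to Sleep Psychology at some point in their patient journey from 1 January 2021 until 31 December 2024". No diagnosis and no minimum score is attached.

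**How patients enter the new pathway.** Under Direct to psychology stepped care, two criteria are joined by and/or. The first is referral for insomnia and/or sleep psychology. The second is "suboptimal adherence to OSA treatment including continuous positive airway pressure therapy (CPAP) or mandibular enhancement splint (MAS) if medical management has been already optimised". Either is enough. The same section has every sleep-psychology referral complete the initial assessment, with the outcome measures.

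**What is tested.** Under Patient-related outcomes: "Patient-related primary outcomes will test non-inferiority in change scores on key clinical outcome measures from pre- to post- intervention". The scales are ISI, DASS-21, K10 and EQ-5D-5L; none measures treatment adherence. Under Statistical analysis: "the criteria adopted to determine non-inferiority will be if the upper bound 95%CI on each clinical outcome measure was less than the minimal clinical important"; the limit that this sentence goes on to name is the MCID.

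**The responder target.** Table 1 (RE-AIM, Effectiveness) reads: "MCID is achieved on outcome measures by > 80% patients at each level".

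**The only ISI figures.** "a score of 11 is indicative of likely meeting criteria for an insomnia disorder in clinical trials and a change score greater than 8", the latter described as the minimally important difference. The threshold of 11 is mentioned but is used neither for entry nor to define an analysis. K10 scores under 20 are described as low distress.

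**The concern.** A symptom-scale non-inferiority test can detect harm only in patients who have improvement to lose. The stated rule lets in patients who may have little or none on the scale being tested:

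- An adherence referral may have a low ISI.
- An insomnia patient may have a K10 or DASS-21 score in the normal range.

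If such patients change little under both models, they pull the between-model difference towards zero. For a non-inferiority test that is the favourable direction. The new model could then be called non-inferior although patients with insomnia lose as much as the margin.

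The same patients count in the denominator of the >80% target but cannot reach the numerator. A missed target might therefore reflect case mix and not treatment.

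**Working it through.** **The plan's own figure.** The article gives no sample size or power for non-inferiority or for the >80% target. Its one power statement (220 patients, four groups, Cohen's f 0.25, 80%) concerns wait times. It recomputes to 88%, a conservative discrepancy with no bearing on this point.

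**Step 1: room to change.**
- ISI has 7 items scored 0 to 4, so its floor is 0. A patient at 8 or less cannot change by more than 8. A patient at 11 must fall to 2 or less.
- K10 has 10 items scored from 1, so its floor is 10. A patient at 19 can fall by at most 9.
- The article gives no MCID value for K10 or DASS-21, so no equivalent cut-off can be computed for them.

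**Step 2: dilution.** Let p be the share of patients who cannot improve (mean change 0 in both periods) and d the true loss among the rest. If p is the same in both periods:

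observed loss = (1-p) × d + p × 0 = (1-p) × d.

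For the observed loss to equal a margin of 8, the true loss must be 8/(1-p): 8.9, 10.0 and 11.4 points at p = 10%, 20% and 30%.

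**Step 3: chance of declaring non-inferiority when d equals the margin M.**
- From the article: about 110 per period; upper bound of the 95% CI below the MCID, read here as a two-sided interval.
- Assumed: SD of change 7; M = 8, taken from the ISI description; p.
- SE = 7 × √(2/110) = 0.944; half-width = 1.96 × 0.944 = 1.85.
- P = Φ((8 - 1.85 - 8(1-p)) / 0.944).

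| p | P, SD 7 throughout, M = 8 | P, mixture, M = 8 | P, mixture, M = 4 |
|---|---|---|---|
| 0 | 2.5% | 2.5% | 2.5% |
| 10% | 13% | 13-20% | 6-8% |
| 20% | 40% | 40-59% | 13-18% |
| 30% | 72% | 74-90% | 24-34% |

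The mixture columns assume SD 5 to 7 in patients who can improve, SD 2.5 in the others and a mean improvement of 10 under the old model. The per-period variance is (1-p)SD₁² + p·2.5² + p(1-p)m², with m = 10 (old) and 10 - d (new). The margin of 4 is an assumption used to show sensitivity.

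**Step 4: unequal shares.** Observed loss = (1-p_old) × 10 - (1-p_new) × (10 - d). With d = 0:
- p_old = 10%, p_new = 20%: 9 - 8 = 1 point of spurious loss.
- p_old = 20%, p_new = 10%: 8 - 9 = -1, a spurious gain.

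**Step 5: responder target.** The best possible response at a level is 1-p. To reach 80% overall, the response among patients who can improve must be 0.80/(1-p): 84% at p = 5%, 89% at 10%, 94% at 15% and 100% at 20%. A target of more than 80% is impossible once p is 20% or more at that level.

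**The case against.** **Adherence referrals are not shown to lack insomnia.** A reader might infer from the adherence criterion that these patients have no insomnia or distress. The documents do not say so. The Background discusses comorbid insomnia and sleep apnoea, and Level 3 describes adherence work as an addition to CBTi for patients with comorbid apnoea. The criterion permits patients without insomnia but does not show that they are many. This stands, and p is unknown.

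**The target is not shown to be out of reach.** That reading needs at least 20% of a level's patients to lack room, which nothing in the article establishes. For ISI the problem would fall mainly on Levels 3 and 4, since Levels 1 and 2 are insomnia programmes. For K10 and DASS-21 it can arise at any level, because insomnia patients without distress are also near the floor. The target is also a RE-AIM benchmark, not a test.

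**The bias need not favour the new model.** This is a non-randomised before-after comparison, and Step 4 shows that a shift in case mix can push either way. This stands.

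**The margin of 8 is an inference.** Statistical analysis says only MCID, and the article links a change above 8 to marked improvement or remission. With a margin of 4 the inflation is much smaller, though still present.

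**The question is service-wide.** Aims and objectives speak of patients referred to the service, and Participants defends broad criteria for real-world relevance. Analysis sets may also be detailed in a SAP. That is a good reason to keep the all-patient comparison. It does not make that comparison sensitive to a loss among patients who can improve, and the article itself fixes the population, the rule and the target.

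**Diagnosis is a candidate covariate.** Adjustment addresses differences in case mix between periods. As a main effect it still yields one model effect averaged over both kinds of patient, so it does not undo the dilution. The moderation analysis in Table 1 is not the decision test.

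**Conclusion.** The point holds in conditional form. The non-inferiority rule and the >80% target have no baseline condition, while the entry criteria allow patients who may have little room to change on the scale tested. Where the share of such patients is similar in both periods, a real loss is shrunk to (1-p) of its size, whatever the margin.

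The size depends on p, which the article does not give. With 110 per period, SD 7, a margin of 8 and a true loss of 8, the chance of wrongly declaring non-inferiority goes from 2.5% to 13%, 40% and 72% at p = 10%, 20% and 30%. With a margin of 4 and SD 5 to 7, it is about 6-8%, 13-18% and 24-34%. The responder target becomes harder at any p above zero and impossible at a level only from 20%.

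The article does not support saying that the adherence group has nothing to improve, that the target cannot be met, or that the bias always helps the new model. The gap should be closed because the rule allows the dilution and nothing stated limits it.

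**What to change.** - Keep the all-patient comparison for the service-level question.
- Before non-inferiority is claimed on a scale, require that it also hold in patients with a raised baseline score on that scale, defined identically in both periods: ISI 11 or more, K10 20 or more, DASS-21 subscale above the normal band. These cut-offs use the article's own descriptions.
- For the >80% target, count in the denominator only patients whose baseline score leaves room for the MCID change. For ISI, with a change greater than 8, that means a baseline of at least 9. For K10 and DASS-21 it follows once an MCID value is fixed.
- Report adherence-only referrals separately.

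**Cost.** A few sentences on analysis sets; the baseline scores are already part of the initial assessment. The price is fewer patients and a wider interval. If, for illustration, 20% fell outside the restricted set, 88 per period would remain, and at SD 7 the half-width would grow from 1.85 to 1.96 × 7 × √(2/88) = 2.07.
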